**Table 2 Tab2:**

Research design

### Study aims

Study design was guided by the following aims:*Primary Aims*: Assess the superiority of DBT-J over supportive group therapy in (a) decreasing risk of future criminogenic behavior and (b) increasing psychosocial functioning.*Secondary Aim*: Assess the superiority of DBT-J over supportive group therapy in improving secondary treatment targets (i.e., suicide-related thoughts and behaviors, criminogenic thinking, psychopathic personality traits, psychological distress, emotion dysregulation, posttraumatic stress, substance use, case management needs, quality of life, resilience, and criminal recidivism).*Exploratory Aim 1*: Assess for differential efficacy of DBT-J across VCLI subgroups (i.e., violent versus nonviolent most recent offense type, presence/absence of a substance use disorder, and presence/absence of a severe mental illness).*Exploratory Aim 2*: Assess long-term impact of DBT-J participation (versus participation in supportive group therapy) on primary efficacy outcomes.

### Participants

Veterans will be recruited via referral from local mental health providers, VA VJP Specialists, treatment court providers, and local Veteran service organizations and via self-referral through mail-based recruitment. To be considered for inclusion, Veterans must be aged 18 + ; able to provide consent (i.e., have capacity to understand the study’s purpose, risk, and benefits and make an informed decision about participation); and have a recent history of criminal-legal involvement, defined as criminal arrest, order of protection, or incarceration within two years prior to participation and/or supervision by probation or parole at the time of enrollment. Exclusion criteria include limited English proficiency; inability to tolerate group therapy format; concurrent enrollment in another clinical trial; concurrent enrollment in interventions based in the RNR model (e.g., MRT) or DBT; and prior participation in DBT-J. Using similar inclusion/exclusion criteria, prior studies have yielded VCLI samples that are predominantly male with notable heterogeneity in race, ethnicity, age, presenting mental health concerns, and criminal-legal history [20, 35]. To maximize generalizability of results to the heterogeneous population of VCLIs, no inclusion/exclusion criteria related to psychopathology and/or VA eligibility will be used. VCLI experience a range of psychosocial needs [7], and many are not eligible for comprehensive VA care due to discharge status or other barriers [46]. Previous trials have successfully enrolled VCLIs across the psychosocial need spectrum, including those with active suicidal ideation, homelessness, psychotic disorders, and severe substance use [20, 35], suggesting feasibility of this flexibility in inclusion/exclusion criteria.

Consistent with previous DBT-J trials [20, 35], we anticipate a dropout rate of 20% during the intervention period, resulting in a final sample size of approximately 160 at post-treatment. Participants are considered to have dropped out of participation after missing four consecutive group sessions. There are otherwise no attendance requirements for participation.

### Study design

#### Study conditions

Veterans in the DBT-J condition will receive 16 weeks of manualized DBT-J programming, including weekly 1-h group therapy, biweekly 30-min individual case management (20 h of total intervention), routine assessments that guide intervention, and provider participation in a DBT-J consultation team as described above. See Table 3 for schedule of intervention and assessment delivered in the DBT-J condition.

**Table 3 Tab3:** DBT-J treatment & assessment schedule

Group Skills Module	Week	Skill(s) Introduced	Other
N/A	Pre-Tx	N/A	Assessment
Introduction	1	Observing Limits	
Mindfulness Skills	2	Mindfulness Introduction	Case Management
	3	Wise Mind & Dialectical Thinking	
Emotion Regulation Skills	4	Mindfulness of Self	Case Management
	5	Emotional Schemas & Self- Validation	
	6	Thinking Errors	Case Management
	7	Check the Facts & Opposite Action	
	8	Self-Soothe	Assessment;Case Management
Goal Directedness Skills	9	Values Clarification	
	10	Mindfulness of Goals	Case Management
	11	Problem Solving	
	12	Distress Tolerance & Acceptance	Case Management
Interpersonal Skills	13	Prosocial Assertiveness	
	14	Mindfulness of Others	Case Management
	15	Building & Maintaining a Prosocial Support Network	
Termination	16	Relapse Prevention	Assessment;Case Management

The comparison condition will provide 16 weeks of clinician-facilitated, supportive group therapy. Sessions will occur weekly and last 75 min (20 h of total intervention), allowing for equivalence in total intervention time across conditions. Consistent with the common factors approach to building comparison psychotherapy conditions [47, 48], supportive group sessions will emphasize building alliance between group members and clinicians; clinician expressions of empathy; clear expectations regarding group participation; adaptation to the target population; and providing opportunity to discuss feelings, concerns, and problems. The clinician facilitator will serve to point out common themes and encourage group participation. Sessions will have no preplanned agenda or structured exercises and will not include elements considered specific to DBT-J (i.e., theoretical foundations in RNR, DBT, and/or SDM models, manualized approach, clinician-introduced and/or guided rehearsal of behavioral skills, or provision of individualized case management).

Both conditions will prioritize supporting the needs and experiences of VCLIs, have a closed-group format, and have an enrollment cap of 8 members per group, allowing Veterans to build meaningful relationships with other group members throughout the treatment period. Both will also be delivered via telehealth to ensure program accessibility regardless of participants’ housing status, transportation barriers, or physical location. All interventions will be provided as an adjunctive service, allowing Veterans to continue care with outside providers throughout their participation in the clinical trial. Information about study participation will be documented in VA electronic medical records to inform outside treatment planning and ensure continuity of care. Following completion of the 16-week intervention period, Veterans will continue treatment as usual with their outside providers for the 32-week observation period.

#### Training & fidelity monitoring

Prior to delivering trial interventions, all providers will participate in a comprehensive, 12-h training in the DBT-J and supportive group therapy interventions. Training includes didactic orientation to theoretical basis and intervention strategies of each intervention and role play exercises to develop and strengthen relevant clinical competencies. Given the unique needs of VCLI and previously documented barriers to implementing forensic-oriented services in VA settings, training also actively identifies and combats commonly held stigmas toward criminal-legal involvement, antisocial behavior, and personality disorders and emphasizes therapeutic engagement strategies, suicide risk assessment and management protocols, and strategies for managing group dynamics over a virtual platform. All research staff involved in provision of study assessments similarly complete standardized trainings, including didactics, role play exercises, and coding of training tapes, prior to delivering any study assessments.

A randomly selected 20% of group (DBT-J and supportive group therapy conditions) and case management (DBT-J condition) sessions will be recorded and reviewed by an independent rater to assess fidelity to treatment protocols. Ratings will be guided by objective scales designed to assess core features of program structure, content, and treatment principles. Providers must maintain an average of 4 out of 5 (some minor violations to adherence) or above on the fidelity scale to demonstrate adequate fidelity. Providers receiving scores of 3 or lower will receive rehabilitative supervision and constant fidelity monitoring until fidelity is re-established.

### Assessment of treatment efficacy

#### Participant characteristics

Demographics assessment will include participant self-reported age, sex, gender, race, ethnicity, sexual orientation, socioeconomic status, employment status, disability status, educational attainment, relationship status, and religious affiliation. Chart and records review, including review of Veterans’ VA medical charts and official criminal history records, will be used to assess history of suicide-related behaviors and history of criminal-legal involvement.

The Level of Service / Case Management Inventory (LS/CMI; [31] will be used to assess risk of future criminal behavior. The LS/CMI is a semi-structured interview assessment based on the RNR model of criminal behavior. It has been widely validated, with the total score as a good predictor of later criminal behavior [49]. Scores are interpreted through comparison against normative data of over 150,000 North American offenders [31].

The Columbia Suicide Severity Rating Scale (C-SSRS; [50]) will be used to assess history of suicide-related behaviors, including suicidal thoughts and behaviors. The C-SSRS is a semi-structured interview that assesses prevalence, recency, and nature of prior suicide-related behaviors. It has been widely used in both VA- and civilian-based settings and demonstrates strong inter-rater reliability and validity in Veteran samples [51, 52].

Mental health diagnosis will be assessed using the Quick Structured Clinical Interview for DSM-5 (QuickSCID-5; [53], and the Structured Interview for DSM-IV Personality (SIDP-IV; [54]. Each is a semi-structured interview to assess for mental health conditions according to established diagnostic criteria.

#### Primary efficacy outcomes

To inform primary aim analyses, participants will complete measures of risk for criminal behavior and psychosocial functioning at all assessment timepoints. Risk for criminal behavior will be assessed using the LS/CMI, described above. Psychosocial functioning will be assessed using the Inventory of Psychosocial Functioning (IPF; [32], an 80-item, self-report instrument measuring functional impairments in romantic relationships, family relationships, work, friendships and socializing, parenting, education, and self-care. Scores are interpreted through comparison to normative data of Veterans [55]. Previous research suggests the IPF to have strong construct validity, concurrent validity, internal reliability, and test–retest reliability [55].

#### Secondary efficacy outcomes

To measure secondary outcomes, participants will complete a range of self-report measures, including the Beck Scale for Suicidal Ideation (BSS; [33], Screen for Nonsuicidal Self-Injury (SNSI; [56], The Measure of Criminogenic Thinking Styles (MOCTS; [57], Triarchic Psychopathy Measure (TriPM; [58]), Patient Health Questionnaire-9 (PHQ-9; [59], PTSD Checklist for DSM-5 (PCL-5; [60], Difficulties in Emotion Regulation-18 (DERS-18; [61], Alcohol Use Disorders Identification Test (AUDIT; [62]), Drug Abuse Screening Test (DAST-10; [63], DBT-J Case Management Checklist [64], Quality of Life Enjoyment and Satisfaction Questionnaire—Short Form (Q-LES-Q-SF; [65]), and Connor-Davidson Resilience Scale (CD-RISC; [66]). To complement these assessments, a chart and records review will be completed by an independent rater to assess for nature and total duration of VA-based mental health care received, presence and frequency of suicide-related behavior documented in VA electronic medical records, and presence and frequency of criminal recidivism (defined as new arrest, violation, order of protection, or incarceration) occurring during the study period.

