#### Assessment

Periodic assessments throughout the course of DBT-J participation allow for measurement-based care, consistently shown to improve treatment effectiveness [30]. Assessments include, for example, previously validated measures of criminogenic risk (e.g., The Level of Service / Case Management Inventory; [31], psychosocial functioning (Inventory of Psychosocial Functioning; [32], and suicide risk (e.g., Beck Scale for Suicidal Ideation; [33]. Assessment results are shared with participating VCLI during individual case management sessions, documented in Veterans’ electronic medical records, and used to guide collaborative treatment and case management planning.

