### DBT-J and suicide risk

The structure and content of DBT-J directly targets overlapping risk factors for antisocial behavior and suicide by: (a) building and strengthening behavioral skills for observing limits, mindfulness, emotion regulation, goal directedness, interpersonal effectiveness, and relapse prevention; and (b) facilitating connection to services and resources that reinforce use of adaptive skills. In early DBT-J trials, one-third of participating Veterans had a history of attempting suicide, and one-third were experiencing suicidal ideation upon program admission [20, 35]. Although analyses were underpowered to detect statistically significant effects, Veterans who completed the program experienced, on average, moderately sized (*d* = 0.30–0.88) improvements in multiple suicide risk factors across the course of treatment, including substance use, psychological distress, and quality of life [35].

DBT-J providers utilize a formal suicide risk assessment and management protocol designed for Veteran samples and VA contexts [36] to facilitate ongoing risk monitoring and efficient, therapeutic responses to acute changes in VCLI suicide risk. Comprehensive suicide risk assessments prior to program entry provide an initial conceptualization of VCLI acute and chronic risk for suicide (i.e., immediate risk and propensity toward increases in immediate risk, respectively). Ongoing monitoring of risk and protective factors is then used throughout the course of the VCLI’s participation in DBT-J to guide suicide risk assessment and management. Notable changes in risk and/or protective factors (e.g., increase in psychosocial stress, decrease in social support) prompt more structured suicide risk assessment and management strategies as necessary to promote VCLI safety. Various VA-based supports, such as those offered by the Veterans Crisis Line, VA Suicide Prevention Coordinators, and other behavioral health providers, are also integrated into suicide risk management efforts to promote effective, sustained risk mitigation.

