## Randomized clinical trial

A multisite randomized Stage III clinical trial will be conducted to assess the efficacy of DBT-J. A total of 200 Veterans will be recruited across three regions in the U.S. (VA VISNs 2, 19, and 21) over three years (2024–2026; anticipated date of recruitment completion, June 30, 2026). Random assignment, stratified by region and generated using an electronic random number generator, will be used to assign participating Veterans to DBT-J or a supportive group therapy condition. Assignment will be completed immediately after enrollment and available only to the PI and individuals involved in intervention delivery; assignment is masked from individuals involved in assessment completion. Veterans will receive 16 weeks of assigned intervention followed by a 36-week observation period. To inform evaluations of treatment efficacy, participants will also complete assessments in 8-week intervals during the intervention period beginning at baseline and 12-week intervals during the follow-up period (6 times total). See Table 2. All protocols were developed in accordance with the Declaration of Helsinki and have been approved by the VA Central Institutional Review Board; protocols and analysis plans are pre-registered through clinicaltrials.gov (NCT05974553, registered July 26, 2023). All participants will provide informed consent prior to participation. To preserve participant confidentiality, individual participant data will not be shared with anyone outside of the immediate research team.

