#### Assessment protocol

Each of the six assessment timepoints will include a combination of semi-structured interviews completed via video call (including LS/CMI at all timepoints, C-SSRS at baseline and final follow-up, and QuickSCID and SID-P-IV at baseline) and self-report questionnaires self-administered via Qualtrics. See Table 4. To minimize bias in assessment, all interviews will be completed by evaluators who are blind to participant condition. Veterans will receive monetary compensation ($75) for each completed assessment; a completion bonus ($75) will also be provided at the end of study participation to participants who complete all assessment timepoints to encourage retention throughout the follow-up period. A random 20% of interviews will be recorded and reviewed by a second rater to assess fidelity to assessment administration protocols and determine inter-rater reliability.

**Table 4 Tab4:** Projected assessment schedule

Assessment	Construct	Baseline	8 weeks	16 weeks	28 weeks	40 weeks	52 weeks
Participant Characteristics							
Demographic Assessment	Demographic background	X					X
Chart & Records Review	Psychiatric treatment history, Military service history, Suicide-related behavior history, History of criminal-legal involvement						X*
QuickSCID / SID-P-IV	Mental health diagnoses	X					
C-SSRS	Suicide-related behavior history	X					X*
Primary Outcomes							
LS/CMI	Risk for criminal behavior, History of criminal-legal involvement	X	X	X	X	X	X
IPF	Psychosocial functioning	X	X	X	X	X	X
Secondary Outcomes							
BSS	Risk for suicide-related behavior	X	X	X	X	X	X
SNSI	Non-suicidal self-injury	X		X			X
DERS-18	Emotion regulation difficulties	X	X	X	X	X	X
TriPM	Psychopathic personality traits	X		X			X
MOCTS	Criminogenic thinking style	X		X			X
PHQ-9	Psychological distress	X	X	X	X	X	X
AUDIT	Alcohol use	X	X	X	X	X	X
DAST-10	Non-alcohol substance use	X	X	X	X	X	X
DBT-J CM Checklist	Case management needs	X	X	X	X	X	X
Q-LES-Q-SF	Quality of life	X	X	X	X	X	X
CD-RISC	Resilience	X	X	X	X	X	X
PCL-5	PTSD symptom severity	X		X			X

^*^Or at time of study termination

A data safety monitoring board (DSMB) comprised of research psychologists with experience in high-risk Veteran populations and intervention development research will aid in monitoring ongoing data collection to evaluate for potentially adverse effects of study participation. Collected data will be shared with the DSMB at least quarterly or within 48 h of an adverse event, whichever occurs first.

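### Masking of the chart-review outcome on suicide-related behaviour is not secured, and its ascertainment may differ by arm

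*Protocol article*

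**What the plan says.** The section Randomized clinical trial limits knowledge of assignment to the principal investigator and intervention staff, and says that "assignment is masked from individuals involved in assessment completion". The section Assessment protocol makes this explicit for one mode of assessment: "all interviews will be completed by evaluators who are blind to participant condition".

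The section Secondary efficacy outcomes adds a further source: "a chart and records review will be completed by an independent rater to assess for nature and total duration of VA-based mental health care received". The same review covers "presence and frequency of suicide-related behavior documented in VA electronic medical records" and criminal recidivism. The rater is called independent; the article does not say blind.

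Two places describe study material in that record. Under Study conditions: "Information about study participation will be documented in VA electronic medical records to inform outside treatment planning and ensure continuity of care". Under Assessment, in the description of DBT-J, results are "documented in Veterans’ electronic medical records, and used to guide collaborative treatment and case management planning", and the Beck Scale for Suicidal Ideation (BSS) is one of the examples.

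Study conditions rules individualized case management out of the comparison arm. Table 3 lists it in DBT-J at weeks 2, 4, 6, 8, 10, 12, 14 and 16, which is eight contacts. The section DBT-J and suicide risk says of the programme: "Ongoing monitoring of risk and protective factors is then used throughout the course of the VCLI’s participation in DBT-J".

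The Data analysis plan tests suicide attempt as a dichotomous endpoint by Poisson regression with robust error variance. It names no data source for it.

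**The concern.** Two separate problems can follow.

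**Masking.** A rater who must establish what mental health care a Veteran received has to read the treatment entries. A charted study case-management contact identifies the arm, because only one arm has such contacts. Deciding whether a charted episode counts as suicide-related behaviour or as an attempt takes judgement, and a rater who knows the arm can be influenced in either direction.

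**Ascertainment.** DBT-J adds private individual contacts that can generate chart entries, and these sessions also help connect Veterans to VA services. The comparison arm meets in groups only. The same event could be disclosed and charted more often in DBT-J, which would raise its apparent event count and work against it.

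Suicide-related thoughts and behaviours are a named secondary aim. Of the sources listed under Secondary efficacy outcomes, the chart review is the only one that covers suicidal behaviour: the BSS measures ideation and the SNSI measures nonsuicidal self-injury. The C-SSRS interview appears in Table 4 under participant characteristics, so a reader cannot tell whether it feeds the suicide-attempt endpoint.

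**Working it through.** **The plan's own figure.** The only calculated figure in the article is the sample size for the primary outcomes. A two-sample t-test with d = 0.50, two-sided α = 0.025 and 80% power needs 77.3, so 78 per arm, against 80 stated; power at 80 per arm is 0.815. With 20% dropout, 160 / 0.80 = 200. This reproduces and is unaffected by the present point. The article gives no suicide-attempt rate and no figure for completeness of charting.

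**Masking, passages side by side.**

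1. Assessment staff are to be masked (Randomized clinical trial).
2. Explicit blinding names interviews only (Assessment protocol).
3. One rater codes both care received and suicide-related behaviour (Secondary efficacy outcomes).
4. The record holds participation information (Study conditions) and DBT-J assessment results (Assessment).
5. Case management exists in DBT-J only (Study conditions, Table 3).

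Items 3 to 5 together mean that carrying out the review as described can reveal the arm. Item 1 is then a statement without a stated means of holding for this outcome.

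**Ascertainment, illustration under assumptions.** Let s_D and s_C be the shares of true events that are charted in DBT-J and in the comparison arm. With no false-positive coding:

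observed RR = true RR × s_D / s_C

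*Gap lasting all year:*

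- s_D = 0.90, s_C = 0.70: 0.90 / 0.70 = 1.29. A true RR of 1 appears as 1.29; a true 0.70 appears as 0.70 × 1.29 = 0.90.
- s_D = 0.80, s_C = 0.70: 0.80 / 0.70 = 1.14. A true 1 appears as 1.14; a true 0.70 appears as 0.80.

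*Gap confined to the 16 treatment weeks of 52, events spread evenly:* s_D = s_C + gap × 16/52.

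- Gap 0.20: s_D = 0.70 + 0.20 × 16/52 = 0.762. Null RR = 0.762 / 0.70 = 1.09; a true 0.70 appears as 0.76.
- Gap 0.10: s_D = 0.70 + 0.10 × 16/52 = 0.731. Null RR = 1.04; a true 0.70 appears as 0.73.

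**Effect on the test.** Take 100 per arm, equal true risk, two-sided 5% level and the normal approximation, and ask how often the test would be significant against DBT-J (nominal 2.5%).

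- Gap of 0.90 vs 0.70 all year: 5.5%, 7.5% and 9.5% at true risks of 5%, 10% and 15%.
- Gap confined to 16 weeks, true risk 10%: charted risks 0.0762 and 0.0700, standard error √[(0.0762 × 0.9238 + 0.0700 × 0.9300) / 100] = 0.0368, z = 0.0062 / 0.0368 = 0.17, and Φ(0.17 − 1.96) = 3.7%.

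The risks and sensitivities are assumptions; none comes from the article.

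**The case against.** The strongest case against has five parts.

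- **Nothing says that the rater is unmasked.** The article does not say that the participation note names the arm or that the charts are unredacted, and preparation of an extract is detail that an article may leave to the full protocol. This stands against the stronger reading, which a reader might infer, that the outcome is simply unmasked. It does not remove the point: the article itself gives one rater both tasks in one record and limits explicit blinding to interviews.
- **A blinded source exists.** The C-SSRS is given by blinded evaluators at baseline and at 52 weeks or study termination, and the chart review is introduced as a complement to other assessments. This is a real mitigant. It does not settle the matter, because the C-SSRS is not listed as a secondary outcome and the endpoint has no named source.
- **The arms are alike in several respects.** Each gets 20 hours of intervention and the same assessment schedule. All providers are trained in both interventions and in suicide-risk assessment and management, and participation is charted in both arms. The article does not say that comparison-arm scores stay out of the chart or that comparison clinicians do not monitor risk. So unequal observation is plausible, not established; case management is the one clear difference in contact.
- **The extra contacts last 16 weeks.** Applying a gap to the whole year needs a further argument, such as lasting VA contact prompted by case management. This stands, and it is why both windows are shown.
- **Recidivism is mostly recorded legal events.** Official criminal history records are part of the review, according to Participant characteristics. The concern is weaker there.

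**Conclusion.** The concern holds in a limited form: for the chart-review outcome on suicide-related behaviour, masking is not secured and ascertainment may differ by arm. A reader might go further and infer that the outcome is neither masked nor equally observed, or that a real benefit would be reversed. The article states neither of the first two. As to the third, a true risk ratio of 0.70 stays below 1 in every scenario worked above (0.73 to 0.90).

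The size is unknown. Under the assumed 90% vs 70% charting, the spurious risk ratio lies between about 1.09 (gap in treatment weeks only) and 1.29 (gap all year). In that direction it works against DBT-J and would not create a false claim of efficacy. Bias from a rater who can see the arm has no predictable sign.

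The reach is limited as well. The outcome is secondary, the rules for superiority and efficacy rest on the primary outcomes, and the LS/CMI interviews are explicitly blinded. The change is worth making because suicide-related behaviour is a named aim and most of the bias can be avoided before the charts are read.

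**What to change.** 1. Have a team member other than the event rater tabulate the VA mental health care received.
2. Give the event rater an extract with study-intervention notes, study encounters and study score reports removed, and state in the protocol that this rater is masked.
3. Code recidivism from the official criminal records, without chart access.
4. In the Data analysis plan, define the suicide-attempt endpoint with the blinded C-SSRS as main source and the masked chart review as complement.
5. Report a sensitivity analysis that excludes events documented only by study providers, and keep those events in safety reporting.

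Exclusion of study-provider events belongs in a sensitivity analysis and should not be the sole definition. It discards real events, and it does not remove differences that arise when case management brings DBT-J Veterans into more contact with other VA services.

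The cost is modest filtering work by existing staff and a few protocol sentences. Outside notes that mention the study may still sometimes reveal the arm, so masking will be better but not perfect.
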